## **2. The Proposed Trial**

### *2.1 What is the proposed trial design? E.g. Open-label, double or single blinded, etc.*

The study will use a cluster-randomised controlled design to test the effects of personality-targeted interventions on substance use and cognitive outcomes. Thirty-two schools (cluster) will agree to conduct annual surveys for 5 years with all consenting adolescents who are enrolled in Grade 7 in September 2012. Schools will be randomly assigned to 1) be trained to deliver the intervention programme and assisted in delivering the selective programme to this Grade 7 cohort or 2) assigned to receive training at the end of the trial, so that their corresponding Grade 7 cohort is never exposed to the intervention. Intervention schools will be assisted by research staff in organisation, delivery and evaluation of interventions delivered to their high risk students meeting criteria for personality risk. All schools will be assisted by our research team in arranging and implementing baseline and follow-up assessments at 12, 24, 36 and 48 months post-randomisation (Appendix B-Consort Figure).

This selective intervention involves screening all students in the first term of their Grade 7 year on personality dimensions linked to risk for substance misuse. Those scoring one standard deviation above the school mean on one of the following four dimensions will be invited to participate in coping skills workshops: Anxiety sensitivity, Hopelessness, Impulsivity, Sensation seeking. Due to the confidential nature of the selection criteria, this information will only be revealed to the teachers who deliver the training workshops. Feedback will not be provided to high risk youth or their parents.

This trial does not include a placebo condition, nor do we attempt to control for therapist contact in the control condition to avoid possible iatrogenic effects of an untested placebo intervention, which have been observed with youth interventions [90]. Furthermore, several systematic reviews of school-based interventions do not show natural reductions in youth substance use resulting from inactive group sessions.

This trial will be open-label, as it will be difficult to blind some participants (facilitators and selected students) to the fact that training and interventions are occurring in their schools. However, due to the confidential nature of the selection criteria for the programme, intervention assignment will be masked for unselected peers and teachers who are not directly involved in the delivery of the programme.

This five-year trial will allow us to observe intervention effects on the development of problematic substance use, which naturally progresses from 13 to 17 years of age and typically has an age of onset of first symptoms at 12-13 years. Similarly, linear changes in cognitive development can be detected over a 5-year period [46-48]. Annual

assessment of onset and severity of substance use and cognitive functioning will provide a sensitive design to examine causal hypotheses within the path from early prevention of substance use to cognitive outcomes and future risk for addiction. See Appendix C for study timeline.

## *2.2 What are the planned trial interventions? Both experimental and control.*

The Preventure Programme is the first and only school-based alcohol and drug prevention programme that has been shown to prevent onset and growth in alcohol and substance misuse in British and Canadian youth [25-29]. Unlike universal programmes that tend to universally promote generic coping skills and balance normative attitudes around substance use, this selected personality-targeted approach is based on a etiologic model of addiction outlined and validated by the PI [27, 29, 92, 93], and targets four personality-specific motivational pathways to substance misuse: Hopelessness, Anxiety Sensitivity, Impulsivity and Sensation Seeking, each associated with different motives for substance use [93], drug use profiles [93, 94] and patterns of non-addictive psychopathology [95].

After selection on personality scales (see 2.5), high risk youth are assigned to personality-specific groups and are invited to participate in two 90-minute group sessions facilitated by a trained facilitator and co-facilitator. The interventions are conducted using manuals which incorporate psycho-educational, motivational enhancement therapy (MET, [96]) and cognitive-behavioural (CBT) components, and include real life ‘scenarios’ shared by local youth in with similar personality profiles. In the first session, participants are guided in a goal-setting exercise, designed to enhance motivation to change behaviour. Psycho-educational strategies are then used to teach participants about the target personality variable and associated problematic coping behaviours like avoidance, interpersonal dependence, aggression, risky behaviours and substance misuse. They are then introduced to the CBT model and guided in breaking down personal experience according to the physical, cognitive and behavioural components of an emotional response. A novel component to this intervention approach is the fact that all exercises discuss thoughts, emotions and behaviours in a personality-specific way, e.g. identifying situational triggers and cognitive distortions related to SS specifically. In the second session, participants are encouraged to identify and challenge personality-specific cognitive distortions that lead to problematic behaviours. For more information on the content and components of the intervention, refer to Appendix G and [25-29, 69].

Control participants will receive minimal drug education and this will depend on the school policy and curriculum. Information on other drug and alcohol prevention programmes delivered at the school and the extent to which participants in the study cohort received the intervention will be recorded. To incentivise control schools to remain in the trial, they will be provided with training on the delivery of the programme at later points in the trial, after the study cohort has completed their final outcome assessment in Grade 11.

Training will be offered to up to 4 staff-members per school. Trainees will include teachers, heads of year, school counsellors, and special educational needs staff who either volunteer or are nominated by the Principal to serve as a Preventure facilitator and school contact for the duration of the trial. They will then attend a 3-day workshop reviewing principles of CBT, MET and general counselling involving didactic instruction and role-play exercises. They will also be instructed on the theoretical basis of the programme, how to use the assessment/selection tool, and details of the research protocol, including the rationale and need for strict compliance around confidentiality, randomisation, voluntary participation and parental consent. Following the 3-day workshop, the trainees will receive a minimum of 4-hours supervision and feedback in running through a full intervention from the research therapist. Supervised interventions will be run with groups of Grade 7-8 students who are not involved in the formal trial. For more detail on training, supervision and accreditation of school facilitators see O’Leary-Barrett et al [28], and Appendix G.

## *2.3 What are the proposed practical arrangements for allocating participants to trial groups?*

Randomisation of schools to intervention or control conditions will be on a 1:1 ratio using a restricted randomisation scheme, to match schools on various demographic characteristics linked to substance use. A staggered approach to randomisation, occurring following recruitment of every 10 schools will allow the clinical staff to stagger training and supervision over the course of the first year of the study. [name] and the staff at the Unité de recherche Clinique appliquée (URCA), Ste Justine, will oversee randomisation and will make sure that schools randomised to intervention and control will be matched on SES (private vs. public), size (number of grade seven classes), gender-specificity (mixed, girls-only, boys-only), and language (French vs. English). All students in grades 7 will be invited to take part in the trial, both survey and intervention phases and regardless of risk status. Responses on Substance Use Risk Profile Scale [93] will determine personality risk status (comparisons are made relative to school mean for each personality dimension). All HR students in intervention schools who consent to intervention phase of the study will be invited to take part in interventions delivered by trained school staff. All students, regardless of risk status, will be followed annually until Grade 11.

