## 10. Sample size calculation for the primary outcome

Sample size calculations are conducted according to the sample needed for the primary long-term analyses, namely the onset of substance use disorders 4-years post-intervention in the sub-group of students identified at high-risk in grade 7. As the school (cluster) is the unit of randomisation, the sample size determination accounts for the clustering of students within schools. According to data from a local epidemiologic study and a previous personality-targeted intervention trial, the expected proportion of students with a substance use disorder in grade 11 in the control group is 10%. The minimum detectable reduction is set to 50% (i.e., 10% substance use disorders in grade 11 in the control group versus 5% in the intervention group). Assuming that this proportion per school is approximately normally distributed (i.e., 95% of the schools would fall within two standard deviations of the mean, 10%, 7 %), we obtain a between-cluster coefficient of variation,  $k$ , of 0.35. In addition, we expect 50 students per school (40-45% of the full sample) to be identified as high-risk (average cluster size of 50), following previous personality-targeted intervention studies. With these assumptions (using formula 7.7,), the number of schools (clusters) per arm needed to detect a 50% reduction in the proportion of drinkers (i.e., from 10% to 5%) with 80% power and a false positive error rate of 2.5% is 15, giving a total of 30 schools or approximately 1500 high-risk students. We plan to recruit two additional schools ( $30 + 2 = 32$  schools total) to account for potential attrition at the school-level.

For the secondary outcomes (other measures of substance use, mental health and cognition), we will use the observed effect sizes from the IMAGEN study on 2000 14 year-old European participants who completed neuropsychological assessments. Binge drinkers showed reduced IQ and a greater reward bias on the Passive Avoidance Learning Paradigm^45 relative to non-bingers where observed effect sizes ( $d$ ) for these mean differences ranged

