**15. Confidence intervals and p-values**

All applicable statistical tests will be two-sided and at the 5% significance level, unless otherwise specified, with two-sided 95% confidence intervals presented whenever possible.

**16. Description of any planned adjustments for multiplicity, and if so, including how the type 1 error is to be controlled**

As there is a single primary endpoint, and the secondary endpoints are to be used only in providing additional supportive exploratory information, and no interim analysis on the primary outcome were done, there will be no adjustments for multiple testing.

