### **26.b Adjustments for primary and secondary outcomes**

To take into account the baseline prognostic factors at the cluster (school) level used for DA (c.f. Section Randomisation), all the results will be adjusted for language of the school, and the gender with three categories.

In case of imbalance for a variable at baseline, interaction and confounding effects will be tested according to its clinical significance.

Modification to protocol: Considering that immigration status has a very large protective effect on youth substance use (including in this sample), and that schools in Montreal vary significantly on this variable, we have modified the analysis plan to also include immigration status (immigrant, first generation, second generation) as a covariate.

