##### model estimating linear growth over time #####
```

```
model_depado <- brm(Flagged ~ 1 + DEM_01 + Exp_Group + Language + year
+year:Exp_Group + (1|id+schoolnum),
data = cov_5,
family = bernoulli,
warmup = 1000,
iter = 3000,
cores = 4,
chains = 4,
seed = 123)
sum_model_depado<-summary(model_depado)
```

```

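### The baseline SURPS scores that define the high-risk group are not covariates in the primary model: a missed low-cost improvement with a probably small gain, and not a source of bias

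*Combined protocol and SAP*

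**What the plan says.** **Selection.** A student is high risk if he or she scores 1 SD above the mean of the student's own school on any one of four SURPS subscales (Protocol 2.1 and 2.5; SAP 21). Protocol 2.3 puts it as: "Responses on Substance Use Risk Profile Scale [93] will determine personality risk status (comparisons are made relative to school mean for each personality dimension").

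**Role of the traits.** Protocol 1.3 calls them personality risk factors for substance misuse. Protocol 2.2 describes the four pathways as "each associated with different motives for substance use [93], drug use profiles [93, 94"].

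**Availability.** SAP 19 requires all 23 SURPS items at baseline for a student to be in the mITT population.

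**Adjustment.** SAP 26.b (Adjustments) says "all the results will be adjusted for language of the school, and the gender with three categories", and adds immigration status as a later modification. The R code at the end of the SAP begins "model_depado <- brm(Flagged ~ 1 + DEM_01 + Exp_Group + Language + year" and continues with a year-by-group term and random intercepts for student and school. A second version treats year as categorical. DEM_01 is not defined in the text. Neither version contains a SURPS term.

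**Where SURPS does enter.** Sensitivity 3 (SAP 26.c) tests the interaction of high-risk status with intervention. The predictors for the attrition weights and the imputation variables (both numbered 27.a) are not listed, so SURPS is neither named nor excluded there.

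**Imbalance.** SAP 24.b and 26.b allow further adjustment if a baseline imbalance is seen. Neither names SURPS.

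**The concern.** The cut-off is relative to the school, so the same absolute score can be high risk in one school and not in another. The analysed group also pools four trait profiles. With 31 schools (SAP 20), 15 of them intervention schools (SAP Table 2) and so 16 control, the arms can differ by chance in absolute trait level and in profile mix.

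The sponsor added immigration status because it predicts substance use strongly and varies between schools. The SURPS traits are the plan's own named risk factors, so the same reasoning applies to them. At stake is some power for the 48-month contrast. The present route to extra adjustment is also triggered by what the data show, which leaves discretion that a named covariate would remove.

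**Working it through.** **1. Reproduce the planned sample size.** Inputs from SAP 10: "10% substance use disorders in grade 11 in the control group versus 5% in the intervention group"; k = 0.35; 50 high-risk students per school; 15 schools per arm "with 80% power and a false positive error rate of 2.5% is 15". SAP 15 says "All applicable statistical tests will be two-sided and at the 5% significance level", so 2.5% is read as one-sided.

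c = 1 + (z_α + z_β)² × [p0(1−p0)/m + p1(1−p1)/m + k²(p0² + p1²)] / (p0−p1)²

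- Within-school term: 0.09/50 + 0.0475/50 = 0.00275 (64%).
- Between-school term: 0.1225 × (0.01 + 0.0025) = 0.00153 (36%).
- c = 1 + (1.960 + 0.842)² × 0.00428/0.0025 = 14.44, so 15 per arm. The plan's figure reproduces.
- Power with 15 per arm: Φ(√(14 × 0.0025/0.00428) − 1.96) = 81.6%.

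**2. What a covariate could change.** Multiply the within-school term by (1−R²) and the between-school term by (1−B). R² and B are assumed, because the documents give neither.

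| R² | B | Power | Schools per arm |
|---|---|---|---|
| 0.01 | 0 | 81.8% | 15 |
| 0.05 | 0 | 82.8% | 15 |
| 0.10 | 0 | 84.0% | 14 |
| 0.02 | 0.10 | 83.4% | 14 |
| 0.05 | 0.25 | 86.2% | 13 |

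Scores centred within school can act only on the within-school term (B = 0), and gain 0.2 to 2.4 points. Raw scores can also explain school differences, and gain about 2 to 5 points in the last two rows.

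**3. Logistic model, one trait that does not vary between schools.** 30 schools of 50, rates 10% v 5%, school SD 0.38 on the logit scale, 1,000 runs. For odds ratios per SD of 1.3, 1.5 and 2.0, power goes from 84.3% to 84.6%, 82.4% to 83.3% and 86.9% to 88.0%. The SE of the log odds ratio does not fall (0.243 to 0.244, 0.245 to 0.247, 0.242 to 0.247). The gain comes from the adjusted odds ratio lying further from 1.

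**4. Logistic model with the plan's selection rule.** 15 v 16 schools, about 1,470 high-risk students, control rate about 10%, log odds ratio −0.65, school SD 0.35, correlation between traits 0.2, 800 runs. Two traits (impulsivity and sensation seeking) are prognostic, and raw scores are used.

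| Odds ratio per SD, each trait | Trait ICC 0.05 | Trait ICC 0.15 |
|---|---|---|
| 1.4 | 74% to 76% | 70% to 75% |
| 1.6 | 73% to 77% | 65% to 75% |
| 1.8 | 69% to 72% | 64% to 75% |

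Base power is below 81.6% partly because the assumed effect is smaller: exp(−0.65) = 0.52, against a planned odds ratio of (0.05/0.95)/(0.10/0.90) = 0.47. The Monte Carlo error of one power figure is about √(0.7 × 0.3/800) = 1.6 points.

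A separate 800-run set gave gains of 2.0 and 2.4 points at 1.4-fold, and 7.4 and 11.7 points at 1.8-fold. With 400 runs, 1.2-fold gave −0.4 to +2 points, and 1.8-fold with trait ICC 0 gave about 3. At 1.8-fold with ICC 0.15 the SE does fall (0.261 to 0.239), because raw scores then remove between-school variation.

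**5. The repeated-measures model in the code.** Assumed: 1,400 students, 5 waves, student SD 1.8, no school effect, no between-school trait variation, 48 datasets per scenario. Adding the four traits left the SE of the year-by-group term unchanged (about 0.116 at 1.4-fold, 0.102 at 1.8-fold). The SE of the 48-month contrast fell by under 1% and by about 2–3%. The student intercept already absorbs most of a stable trait.

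**The case against.** The strongest reply is that nothing here is an error. The same selection rule applies in both arms and schools are randomised, so neither the school-relative cut-off nor the mix of profiles biases the comparison. That stands. A reader might infer that omitting SURPS biases the primary result; the documents do not support this.

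A reader might also infer that SURPS is used nowhere. Sensitivity 3 uses SURPS-derived status, and the weighting and imputation variables are unlisted.

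The unadjusted odds ratio lying closer to 1 is non-collapsibility, a difference of estimand and not a defect. That stands too. So does the point that the two-level 48-month model of SAP 26.a was replaced by a Bayesian repeated-measures model (deviation item 6, after Appendix 3), in which the trait adds less. That check had no between-school trait variation, so it does not rule out a gain for the 48-month contrast.

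The imbalance provisions in SAP 24.b and 26.b offer a route to adjustment, but a discretionary one that does not name SURPS.

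Finally, the change is not entirely free. Item 6 shows that data had been analysed. SAP 18.d reports three schools that left after randomisation without launching screening, so SURPS is pre-intervention but not clearly pre-randomisation, in a trial that Protocol 2.1 calls open-label.

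**Conclusion.** The point holds as a missed improvement. No baseline SURPS score or profile is a listed covariate or a term in the primary model code, although SURPS defines the analysed group, is treated by the plan as prognostic, and is already collected.

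For the 48-month contrast the gain is probably small: about 0 to 5 power points under moderate assumptions (odds ratios of roughly 1.2 to 1.4 per SD, or R² up to 0.05). Gains of about 10 points need odds ratios of roughly 1.6 to 1.8 per SD for two traits together with a trait ICC near 0.15. A reader might take that upper figure as an established loss. It is not, because the documents report neither the SURPS–disorder association nor the between-school variation of the traits. The simulations also leave out immigration status, which the plan already adjusts for. Little or no gain is expected for the year-by-group term, and none was shown for secondary outcomes.

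**What to change.** - In SAP 26.b (Adjustments), name the four baseline SURPS subscale scores as covariates for the 48-month substance use disorder comparison. Use raw scores standardised over the whole sample, not centred within school. Leave the selection rule as it is.
- In SAP 24, add SURPS scores and profile mix by arm to the baseline tables. This also lets the reader judge whether recruitment after randomisation made the arms differ.
- Declare the change as post hoc and report the adjusted result beside the planned model.
- Extension to the secondary models is optional.

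The cost is one line in the SAP and four student-level terms, in a sample of roughly 31 × 709/15 ≈ 1,465 students if control schools are of similar size. No new data are needed. The adjusted odds ratio is conditional on SURPS and should be labelled so, with the caveat that SURPS may have been measured after randomisation.

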#### *2.4 What are the proposed methods for protecting against sources of bias? E.g. Blinding or masking..*

The trial coordinator and clinical psychologist overseeing training will not be blind to intervention allocation, but all trial staff who are involved in data acquisition will remain blind. Data will be anonymised; quality control of data will be conducted by staff blind to treatment condition.

This is not a fully double-blind study, but there will be some masking of school allocation and selection of participants. Schools are randomly assigned to intervention or control conditions, and a small number of school staff will be trained in the delivery of these interventions. Due to the targeted nature of the study, in order to avoid any potential effects of labelling attached to students participating in the intervention sessions, most school staff will be blind to the randomisation and risk status of students. Only trained facilitators in intervention schools will be provided with this information, which will be treated as confidential. In addition, all self-report data will be kept confidential and these facilitators will not be responsible for data collection. The general school staff will be informed that the whole year group are taking part in a research project and that some students will be invited to take part in coping skills interventions, however it will be emphasised that the interventions are meant to help youth channel their personality style towards their longer-term goals and will therefore not target students based on problem behaviours.

In order to maintain interest of control schools in this long trial, we will begin to train control schools in the delivery of the programme to subsequent Year 7 cohorts in the third year of this trial (after the study cohort have completed their 36 month assessment). This is the procedure that we used in the Adventure Trial, which did not appear to have any impact on the long-term results of the trial [29]. Training occurs over the course of the year in which 36-month outcomes are assessed at the schools, and schools will be provided with manuals and supervised in the delivery of the programme to the Year 7 cohort of 2016-17 after the final assessment of the study cohort in Year 11, creating a broader perception that the programme is being delivered in all schools.

Another important source of bias is lost to follow-up (LFUP), which can be related to primary and secondary outcomes. Most students drop out of a trial due to graduating from high school and moving to other schools, but this will not be a problem in this trial, as we do not expect to follow-up students beyond Grade 11. We also plan to use specific analytic methods, such as survival analysis, to manage this bias, which allow for assessment of outcome without necessarily requiring follow-up data at every point [26].

